| [name] | Wonkang University College of Korean Medicine | | Assistant professor | | [name] / [[contact]](mailto:[contact]) | | Study design and data analysis consultatio | |
| [name] | Wonkang University College of Korean Medicine | | Graduate student  (Master’s) | | [name] / [[contact]](mailto:[contact]) | | Assist in study design and data analysis | |

1. Roles by affiliation

* Kyung Hee Bi,Che,Dam Korean Medicine Clinic: recruit participants, collect informed consent, perform trial

* Korean Institute of Oriental Medicine: study design and analysis, monitoring, administration

* Wonkang University College of Korean Medicine: study design and data analysis consultation

1. Name and address of trial facility

Trial facility (single-center study): Kyung Hee Bi, Che, Dam Korean Medicine Clinic ([name])

1. Sponsor

National Institute for Korean Medicine Development ([name])

1. Study period

Anticipated study period (1 year from approval by joint IRB. Scheduled to be completed on August 31, 2024)

1. Study participants
2. Recruiting facility

(Single-center) Kyung Hee Bi, Che, Dam Korean Medicine Clinic

1. Number of patients to be recruited

After screening candidates for eligibility, 30 participants who received mSMS will be recruited.

Study participants must meet all of the inclusion and not meet all of the exclusion criteria to be enrolled in the study.

1. Inclusion criteria
2. Adult men and women aged 19–74 years.
3. BP measured from the reference are at time of screening:

- If not taking antihypertensive drugs: 140 mmHg ≤ MSSBP(mean sittingSBP) < 180 mmHg
- If taking antihypertensive drugs: 130 mmHg ≤ MSSBP(mean sitting SBP) < 180 mmHg

1. Voluntarily provide a fully informed consent to provide medical records and personal information for use in the study.

- (*Reference arm is selected based on the process outlined in “12. Observation parameters-B.Measurement items”)
- (*Mean seated BP is defined in “12. Observation parameters-B.Measurement items)

1. Exclusion criteria
2. ≥ 20 mmHg difference in Systolic Sitting Blood Pressure (SSBP) and more than a 10 mmHg difference in Diastolic Sitting Blood Pressure (SDBP) across three consecutive measurements, taken at least 2 minutes apart in both arms
3. Mean seated SBP (MSSBP) ≥ 180 mmHg or mean seated DBP (MSDBP) ≥ 110 mmHg in the reference arm at time of screening

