Patients who express interest in participating will be informed about the study’s purpose, methods, and that there is no additional financial burden for treatment and testing. Those who provide voluntary consent will be enrolled.

The participant recruitment process is as follows: patients with HTN visiting the study facility who qualify per the eligibility criteria and provide consent will be enrolled in the study as part of their treatment process, and their anthropometry and changes in BP and quality of life will be monitored using tests and questionnaire; thus, the participants will be consecutively recruited.

The names and contact details of participating patients will be accessible only to the research team. The PI and sub-investigator will contact each participant individually to arrange their participation schedule.

1. Participant consent

- **Before beginning observational study** The purpose and details of this observational study will be explained in detail, along with the tests and treatments performed as part of the study.

- The informed consent form is collected only when the study participants are given adequate time to understand the purpose, method, risks, and benefits of study participation, and oluntarily agree to participate. - At the initial visit to the healthcare facility, the research team will obtain the informed consent from the participants and enroll them.

- The PI, [name] (Korean medicine doctor), will obtain the informed consent forms.

- Participants do not consent to participate, do not qualify per the eligibility criteria, do not take the modified SMS even once during the observation period even after signing informed consent form and qualifying per eligibility criteria, or refuse to participate during the study period may be **discontinued from the study.**

-The informed consent form will be obtained in a quiet, private space where the investigators can communicate with the study participants without interruptions; it will be a private space within the Kyung Hee Bi, Che, Dam Korean Medicine Clinic. The names and contact information of the participants will only be accessible to the research team.

- The participants are informed that they will not receive any form of disadvantage or impact on their treatment for not participating in the study.

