- The study is conducted under a national research and development project commissioned by the National Institute for Korean Medicine Development (NIKOM) (evidence-generating research as part of Korean medicine innovative technology development project). The research data collected according to the study announcement will be recorded and stored through E-CRF (Mytrial) established by NIKOM and provided to them. Provision of the study data to a third party and use of the data for secondary studies will be permitted only after obtaining a separate consent from from the participants for the purpose.

1. Method
2. Outline of method
3. Study period

Anticipated study period (1 year from approval date. Scheduled to be completed by August 31, 2024)

1. Study site

Kyung Hee Bi, Che, Dam Korean Medicine Clinic; a prospective observational study on patients

1. Study design

Single-group, prospective, exploratory, preliminary observational study

This study is an observational study for preliminary exploration of the therapeutic effects of modified SMS on HTN and for exploration of feasibility for future randomized controlled trial.

1. Study schedule (standard management protocol): 4 clinical assessments

Baseline (wk 0, screening and enrollment, visit 1)

Mid-treatment (4 weeks after beginning dosing of modified SMS) (visit2)

End of treatment (8 weeks after beginning dosing of modified SMS) (visit3)

4-week f/u after treatment (12 weeks after beginning dosing of modified SMS) (visit4)

1. Standard protocol for modified SMS

The participants will undergo the following process per the standard protocol:

When using modified SMS, those receiving any other KM treatments, including acupuncture, pharmacopuncture, and moxibustion, will be excluded

1. Standard herbal medicine prescription protocol

- Compliance with pre-visit instructions:
  After making an appointment for the visit, patients are instructed to fast for 8 hours before the visit, refrain from smoking, drinking, and consuming caffeine the day before the visit, and to visit the clinic between 8–12 AM.
- History taking
- 3D BP waveform test (3-d pulse imaging study), blood test
- Same tests performed at F/u on weeks 4, 8, and 12 after herbal medicine prescription

1. Standard protocol visits

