A study questionnaire will be used to obtain data, and a total of five test parameters will be monitored. The questionnaire and tests will be performed at every visit, and it will take about 30 minutes. The questionnaire and tests will be performed at Kyung Hee Bi, Che, Dam Korean Medicine Clinic, and the PI will be in charge of distributing and collecting the questionnaire and performing tests.

| Item | Screening and enrollment | Treatment phase | | F/U |
| --- | --- | --- | --- | --- |
|  |  | 4wks | 8wks | 12wks |
| Visit | Visit 1 | Visit 2 | Visit 3 | Visit 4 |
| Visit window | 0주 | Week 4 (±7 days) | Week 8  (±7 days) | Week 12  (±7 days) |
| Informed consent | ○ |  |  |  |
| Sociodemographic information | ○ |  |  |  |
| VS and physical examination | ○ | ● | ● |  |
| Compliance with pre-visit instructions | ○ | ● | ● |  |
| Medical history·treatment history·medication history | ○ |  |  |  |
| Inclusion and exclusion criteria | ○ |  |  |  |
| Blood test | ● | ● | ● |  |
| BP and pulse measurement | ○ | ● | ● |  |
| 3D BP waveform test | ● | ● | ● |  |
| European Quality of Life Five Dimension Five Level Scale (EQ-5D-5L) | ● | ● | ● |  |
| Modified SMS prescription and dispensing | ● | ● |  |  |
| Monitoring of herbal medicine adherence and dosage |  | ● | ● |  |
| Monitoring of AEs |  | ● | ● | ● |
| Changes in Medical history·treatment history·medication history ** |  | ● | ● | ● |
| Conclusion of case* |  |  |  | ● |

Table 2. Summary of study data collected by timeline

* Conclusion of case: collected after visits are completed or participant is discontinued

** Changes in Medical history·treatment history·medication history: Collect information upon changes in Medical history·treatment history·medication history since the visit

● Tests performed only on those who qualify per the inclusion/exclusion criteria

eCRF will be identical to the paper-based CRF, and the Mytrial program at NIKOM will be used to establish the eCRF.

Modified intervention records: if the treatment interventions are changed mid-way, the changes will be recorded in the modified intervention record section of the CRF.

Concomitant drugs and treatment: Concomitant drugs and treatment will be recorded in the respective section in the CRF.

1. Management of human-derived materials

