In this study, the results of blood tests performed as part of the standard management protocol used at the study clinic will be analyzed. Thus, no additional blood tests will be performed due to the study, and results from the blood tests performed routinely on the patients per their treatment protocol will be collected and analyzed for the purpose of this study.

Collection of human-derived materials (blood): 35 ㎕ of blood will be collected through a finger puncture and immediately placed in the kit for analysis using a LABGEO PT10 Analyzer.

Analysis of human-derived materials (blood): blood sample will be analyzed using a LABGEO PT10 Analyzer

Disposal of human-derived materials (blood): After analysis, the blood will be placed in a biohazard waste container and will be discarded with other biohazard wastes twice a month by a biohazard waste removal company (Munhwa Green, [name]).

1. Observation parameters
2. Sociodemographic information
3. History taking
4. History
5. Surgical history
6. Medication history

* Information about antihypertensive medication use will be collected.
* If the patient is taking antihypertensive drugs, they are instructed to notify the investigator regarding the dosage of the drug and any changes to the dosage.
* Patients are informed to maintain their normal lifestyle, including exercise and diet.

1. Measurement items
2. Height and VS (excluding BP and pulse): 5 minutes of measurement followed by 15-min rest
3. BP and pulse
   - - 1. Measurement device: electronic blood pressure cuff Omron Healthcare (Model: HEM-9000AI)
       2. Measurement items

- MSSBP (Unit: mmHg)
- MSDBP (Unit: mmHg)
- Pulse (Unit: beats/min)
  - - 1. Measurement method
- **Definition of MSBP:** the average of **three or more measurements** taken with at least 2 minutes apart is used. BP is measured in a straight seated position (seated BP).
- **Arm selection**: BP is measured from both arms if possible, and the arm with the higher BP is selected. Subsequent BP measurements must be taken from the same arm.
- Posture should remain unchanged while measuring BP. A supine or seated position must be maintained for at least five minutes, and a standing posture must be maintained for at least one minute before taking the measurements.

1. Blood test
   - - 1. Measurement device: LABGEO PT10 Analyzer

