       2. Measurement items: Aspatate transaminase(AST), Alanine transaminase(ALT), Gamma glutamyl peptidase(GGT), Total Bilirubin, BUN, Creatinine, Total cholesterol, Glucose
       3. Measurement method

- Refrain from caffeine, alcohol, and tobacco consumption the day before the test
- 8-hour fasting is required before the test; water allowed
- Test takes 10 minutes

1. [**3D Blood pressure and pulse wave test]**: **3d pulse wave imaging device (3D MAC, ㈜ Daeyomedi Co., Ltd., South Korea)**: 10 minutes ( See [Attachment 1])
   - - 1. Pulse strength value and stage (Unit:gf)
       2. Pulse depth value and stage (Unit:gf/cm^2)
       3. Pulse velocity value and stage (Unit:beats)
       4. Pulse shape value and stage (Unit:step)
       5. Radial artery augmentation index(R-AI) (Unit:%)
       6. SBP (Unit:mmHg)
       7. DBP (Unit:mmHg)
       8. Pulse pressure (PP) (Unit:mmHg)
       9. Pulse rate (PR) (Unit:beats/min)
       10. Cardiac output (1 beat) SV (Unit:mL/beat)
       11. Cardiac output (1 minute) CO (Unit:L/min)
       12. Systemic vascular resistance index(SVRI) (Unit:dyn*s/cm^5/m^2)
2. European Quality of Life Five Dimension Five Level Scale (EQ-5D-5L) questionnaire: 5 minutes ( see [Attachment2] )
3. Other

Adverse events and concomitant treatments are monitored per patient’s report and questions at every visit

1. Outcome measurement criteria and method
2. Primary outcome

This study is an exploratory observational study aiming to explore the safety and BP-lowering effetcs of modified SMS prepared and prescribed by Kyung Hee Bi, Che, Dam Korean Medicine Clinic for patients with HTN by comparing SBP before and after treatment.

1. [Changes in MSSBP] use Omron Healthcare HEM-9000AI
   Amount of change in MSSBP at end of treatment (visit 3) compared to the baseline (visit 1)
   - - 1. Null hypothesis (H0): There is no difference in MSSBP between the baseline (Visit 1) and end of treatment (visit 3).
       2. Alternative hypothesis (HA): There is a difference in MSSBP between the baseline (Visit 1) and end of treatment (visit 3).
2. Secondary outcome
3. Amount of change of MSSBP at visit 2 compared to the baseline (visit 1)
4. Amount of change of MSSBP at visits 2 and 3 compared to the baseline (visit 1)
5. Percentage of participants with normalized BP: percentage of patients who achieved normal BP compared to MSSBP/MSDBP measured at each time point (percentage of patients who had a BP of less than 140/90 mmHg at end of treatment)

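### The visit 1 MSSBP that admits the patient is also the primary baseline, so regression to the mean can produce a fall at visit 3 with no product effect

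*Protocol*

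**What the plan says.** - **One visit.** Method, Study schedule, lists "Baseline (wk 0, screening and enrollment, visit 1" as a single assessment. Participant consent adds: "At the initial visit to the healthcare facility, the research team will obtain the informed consent from the participants and enroll them".
- **Entry floors.** Inclusion criteria: "If not taking antihypertensive drugs: 140 mmHg ≤ MSSBP(mean sittingSBP) < 180 mmHg" and "If taking antihypertensive drugs: 130 mmHg ≤ MSSBP(mean sitting SBP) < 180 mmHg". A value of 180 mmHg or more excludes.
- **One pre-dose cuff measurement.** In Table 2 the row "BP and pulse measurement" has an open circle at visit 1. The filled circle is defined as "Tests performed only on those who qualify per the inclusion/exclusion criteria". The blood test, 3D waveform test and EQ-5D-5L have a filled circle at visit 1; cuff BP does not.
- **Arm.** Observation parameters, Measurement items: "BP is measured from both arms if possible, and the arm with the higher BP is selected", and later readings stay in that arm. MSBP is the mean of three or more readings at least 2 minutes apart.
- **Primary test.** The null hypothesis is "There is no difference in MSSBP between the baseline (Visit 1) and end of treatment (visit 3". Data analysis and statistical methods plans a paired t-test or Wilcoxon signed rank test, two-tailed at 5%. There is no control group.
- **Caveat.** Outcome evaluation criteria says that efficacy is hard to determine without a control group. The protocol does not mention regression to the mean, a run-in or a repeat baseline.

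**The concern.** A reading that must pass a floor to count is, on average, above the patient's usual pressure when most of the source population sits in the lower part of the entry window or below it. Visit 3 has no such floor. The mean change then drifts downward without any treatment effect, and a test against zero rejects more often than 5%.

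If the readings that picked the higher arm are also averaged into the baseline, the chance part of the difference between arms adds to the drift. A lasting difference between arms does not, because the same arm is kept.

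The study's purpose is to explore BP lowering by a before-after comparison and to inform a later randomised trial. An inflated fall would mislead that use. It would also raise the response rate (a fall of at least 20 mmHg systolic or 10 mmHg diastolic).

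**Working it through.** **Inputs from the protocol.** Floors 140 and 130 mmHg, cap 180 mmHg, change from visit 1 to visit 3, two-sided 5% paired test, 20 patients with data. The recruitment figure reproduces: 20 / (1 − 0.33) = 29.85, so 30. The protocol gives no effect size, SD or power, so there is no planned change to reproduce.

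**Assumed, not in the documents.** Source mean, between-person SD, visit-to-visit SD (6 to 10 mmHg) and arm-level noise.

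**Step 1: regression to the mean alone (closed form).** With source mean μ, between-person SD σb, within-person SD σw, and total SD σ = √(σb² + σw²), let a = (floor − μ)/σ and b = (180 − μ)/σ. Then

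expected fall = σ × [φ(a) − φ(b)] / [Φ(b) − Φ(a)] × σw²/σ².

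Example: floor 140, μ = 145, σb = 15, σw = 8. Here σ = √(225 + 64) = 17, a = −0.294 and b = 2.059. The selected mean exceeds μ by 17 × (0.382 − 0.048)/(0.980 − 0.384) = 9.5 mmHg. The within-person share is 64/289 = 0.221. The fall is 9.5 × 0.221 = 2.1 mmHg.

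Falls in mmHg for σw = 6 / 8 / 10, with σb = 15:

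| Source mean | Floor 140 | Floor 130 |
|---|---|---|
| 135 | 2.2 / 3.7 / 5.3 | 1.3 / 2.3 / 3.4 |
| 145 | 1.3 / 2.1 / 3.1 | 0.6 / 1.1 / 1.6 |
| 155 | 0.4 / 0.7 / 1.0 | 0 / 0 / 0 |

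The fall vanishes at the middle of the window, (140 + 180)/2 = 160 or (130 + 180)/2 = 155, and reverses above it because of the cap.

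**Step 2: adding arm choice (simulation, zero effect, n = 20, floor 140).** Usual SBP SD 12, visit-to-visit SD 6 to 10, noise of a three-reading arm mean SD 3, and a lasting arm difference of SD 0 or 3 per arm. The higher arm decides eligibility. Rejection comes from the noncentral t distribution with noncentrality fall/(SD of change/√20). For example, 6.4/(13.6/√20) = 2.1 gives 51%.

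| Source mean | Lasting arm SD | Arm-choosing readings are the baseline: fall, rejection | Separate readings are the baseline: fall, rejection |
|---|---|---|---|
| 140 | 0 | 3.9 to 6.4, 45% to 51% | 1.9 to 4.4, 14% to 27% |
| 140 | 3 | 3.3 to 5.7, 33% to 42% | 1.8 to 4.2, 13% to 25% |
| 150 | 0 | 2.6 to 3.7, 21% to 23% | 0.8 to 1.9, 6% to 9% |
| 150 | 3 | 2.0 to 3.0, 15% to 16% | 0.7 to 1.7, 6% to 8% |
| 155 | 0 | 2.0 to 2.5, 12% to 16% | 0.3 to 0.7, 5% to 6% |
| 160 | 3 | 0.6 to 0.9, 5% to 7% | slight rise, 5% |

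With floor 130, source means of 135 to 145 and no lasting arm difference, the combined fall is 2.3 to 5.3 mmHg and rejection 16% to 37%.

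**Step 3: response rate.** With no effect, about 2% to 16% of patients fall by at least 20 mmHg systolic.

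**Step 4: does the planned ANCOVA help?** No. In a single group, adjusting for initial BP and other covariates leaves the mean change at the covariate means unchanged. There is no comparison group from which the shift could cancel.

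**The case against.** The protocol calls itself exploratory, says it is not investigating efficacy, plans descriptive presentation and admits the limits of having no control. Regression to the mean is inherent in any threshold-selected single-group study. This stands, and it lowers the severity. It does not correct the test: a null of zero change at 5% is still stated, and efficacy is still to be judged from improvement over this baseline.

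Three stronger readings are tempting, and the documents do not support them.

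- **That the null is false whatever the source population.** The source mean and SDs are not given. Near the middle of the window the expected fall is small or nil, and above it the cap can reverse the sign.
- **That the baseline certainly contains the arm-choosing readings.** The measurement section gives arm choice and the MSBP definition as separate items, so the arm could be chosen first and MSSBP measured afterwards. The exclusion criterion on three readings in both arms, and the single visit 1 entry in Table 2, point the other way. The text is ambiguous.
- **That an unfamiliar setting raises visit 1 pressure.** Consent is taken at the initial visit, but recruits are people already visiting the clinic. They attend by appointment after fasting and caffeine instructions, and the measurement section requires rest. No such effect is claimed or counted here.

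LOCF may also dilute the result. If the 33% expected not to return enter the FAS with visit 1 carried forward, their change is zero and the mean fall shrinks to about two thirds. Whether they enter depends on how the FAS wording is read. Dilution would not remove the bias.

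**Conclusion.** The concern holds in limited form. One cuff measurement serves as both entry gate and primary baseline, and the zero-change null is biased toward a fall for plausible source means below about 155 to 160 mmHg. The direction follows from the text; the size does not. It rests on the assumed SDs (usual SBP 12, visit-to-visit 6 to 10, arm noise 3) and n = 20.

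- Floor 140, source means 140 to 150, arm-choosing readings used as baseline: a fall of about 2.0 to 6.4 mmHg and 15% to 51% rejection, depending partly on the lasting arm difference.
- Same means, readings already separate: about 0.7 to 4.4 mmHg and 6% to 27%.
- Source means 155 to 160, arm-choosing readings used as baseline: about 0.6 to 2.5 mmHg, with rejection no more than about 16% and close to nominal at the low end.

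This should be fixed rather than must be fixed, because the stated purpose is exploratory. The change belongs in the protocol before enrolment, since a baseline not taken before dosing cannot be recovered.

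**What to change.** 1. **Separate the baseline readings.** At visit 1, use one set of readings to choose the arm and decide eligibility. Then take a separate set of three in the chosen arm before the first dose, and define that set as the baseline MSSBP. Show it in Table 2 as done only in those who qualify. This removes the arm-selection and same-sitting part, about 1.2 to 2.0 mmHg in the simulation, but not the day-to-day part.
2. **Limit the conclusion.** Report the primary change with its confidence interval beside a sensitivity range for the fall expected from regression to the mean under the 140 and 130 floors, with the assumed source mean and visit-to-visit SD stated. Say that rejecting zero change is not by itself evidence of BP lowering. Do not turn one expected fall into a pass/fail threshold, because the trial cannot pin down the source mean or SD.
3. **Add a supplementary contrast.** Report the visit 2 to visit 3 change, which is free of entry selection, and note that it misses any effect already reached by week 4.

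Cost: a few minutes of cuff readings at visit 1, a wording change and a short extra analysis, with no added visit or staff. The reported change will probably be smaller.

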- (Visit) Patients who take herbal medicine prescribed by Kyung Hee Bi, Che, Dam Korean Medicine Clinic are instructed to make f/u visits every 4 weeks for monitoring of AEs and clinical progress. In case of AEs, additional visits may be necessary.

1. Standard protocol tests

- The Standard management protocol at Kyung Hee Bi, Che, Dam Korean Medicine Clinic involves performing 3D BP waveform test and blood tests on patients taking herbal medicines every four weeks. In the present study, only patients taking modified SMS were enrolled. However, additional tests may be performed in cases of AEs.

1. Study intervention: administration of modified SMS per standard protocol

In the present study, we modified the traditional SMS formula used for CVD (ginseng, Ophiopogon japonicus, and Schisandra chinensis) based on clinical experience, classic texts, and experiment findings. We removed ginseng and added Platycodon grandiflorus and Pueraria lobata as well as Dioscorea opposita and Coix lacrymajobi to stimulate digestive functions. The formula consisting of **Pueraria lobata (5.33g), Platycodon grandiflorus (5.33g), Ophiopogon japonicus (5.33g), Dioscorea opposita (2.67g), Coix lacrymajobi (2.67g), and Schisandra chinensis (2.67g) (total 24g; unit g/day)** is referred to as saengmaeksangagambang (modified SMS). This is one of the unique empirical prescriptions used at Kyung Hee Bi, Che, Dam Korean Medicine Clinic. Although in actual practice at Kyung Hee Bi, Che, Dam Korean Medicine Clinic, **certain ingredients may be removed, doses may be adjusted, or other interventions such as acupuncture, may be added depending on the symptoms and disease being treated, such cases were excluded from the analysis in this study.**

- Patients take a 60-mL 70% alcohol-soaked decoction of the modified SMS formula prepared by Kyung Hee Bi, Che, Dam Korean Medicine Clinic twice daily before meals or between meals
- Dispensing of medicine on Visit 1, Visit 2: [number of days until next scheduled visit date (standard 28 days, maximum 35 days) + 3 days]* 2 packs. A standard of 62 packs, up to 76 packs, are packaged in a box or pack, labeled with the patient’s information.
- Participants will return unused medicine at the subsequent visit.
- Returned unused medications will be stored separately for each patient in a box/pack.
- At completion of trial, returned medicines will be disposed of following the facility’s medication disposal procedures.

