- Dose per pack: modified SMS: each pack contains 60 mL containing Pueraria lobata (5.33g), Platycodon grandiflorus (5.33g), Ophiopogon japonicus (5.33g), Dioscorea opposita (2.67g), Coix lacrymajobi (2.67g), and Schisandra chinensis (2.67g) (total 24g; unit g/day).
- Dosage: oral; 2 packs a day
- Treatment period: 8 weeks (56 days) (f/u every 4 weeks)
- Permitted concomitant treatments: Given the observational nature of this study, we will not limit any concomitant treatments and medications while undergoing the SMS regimen, and concomitant treatments will be documented.
  * Use/non-use of antihypertensive drugs will be documented.
  * If antihypertensive drugs are being used, patients are informed to notify the investigator upon changes in the dose and dosage of the drug.
  * Patients are informed to maintain their normal lifestyle, including exercise and diet.
- The dose and dosage of modified SMS used in this trial are identical to those used in actual practice at Kyung Hee Bi, Che, Dam Korean Medicine Clinic.

|  | | |
| --- | --- | --- |
| [figure not shown] | [figure not shown] | [figure not shown] |
| Cold extraction | Vacuum concentration | Concentrate |

Figure 5. Preparation facilities at Kyung Hee Bi, Che, Dam Korean Medicine Clinic and appearance of concentrates

1. Additional interventions, visits, and tests required for study participation per the purpose

The Standard management protocol at Kyung Hee Bi, Che, Dam Korean Medicine Clinic involves performing 3D BP waveform test and blood tests on patients taking herbal medicines every four weeks. In the present study, only patients taking modified SMS were enrolled. **Thus, there are no additional interventions required for participation in this study**

**In case of an adverse event, f/u is needed until the adverse event is resolved. In such cases, additional visits may be necessary.**

In case of an adverse event, additional tests, such as kidney function test, liver function test, and complete blood count, may be performed.

1. Control group, randomization, blinding

This is a single-group study without a control group, so randomization and blinding are not applicable.

1. Summary of study timeline (anticipated duration, place, staff in charge, study procedure)

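### Dispensed packs last 3 days past the booked visit, but visits 2 and 3 may be 7 days late, so an in-window end-of-treatment blood pressure can be read up to about 4 days off drug

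*Protocol*

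**What the plan says.** Section 11.C (Study intervention) dispenses modified SMS at visits 1 and 2 only. The quantity is two packs for each day of "number of days until next scheduled visit date (standard 28 days, maximum 35 days) + 3 days", giving "A standard of 62 packs, up to 76 packs". The dose is "Dosage: oral; 2 packs a day". On leftovers, the same section says: "Participants will return unused medicine at the subsequent visit". It also gives a treatment period of 56 days.

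Table 2 in section 11.F sets visit 2 at week 4 and visit 3 at week 8, each with a window of 7 days either way. Section 11.B asks patients "to visit the clinic between 8–12 AM", so readings are taken in the morning.

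Section 13.A defines the primary outcome as "Amount of change in MSSBP at end of treatment (visit 3) compared to the baseline (visit 1". The change in MSSBP to visit 2 is a secondary outcome. Section 16 admits to the FAS anyone with at least one dose and one measurement of the primary outcome. Neither section sets a limit on time since the last dose.

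**The concern.** The pack totals are correct. The mismatch is between the 3-day reserve inside them and the 7-day lateness that Table 2 tolerates. The reserve is counted from the booked date, and leftovers from the first interval are handed back, so they do not add to the second. A patient who comes 4 to 7 days after the booked date without notice can be out of drug and still in window.

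The primary result is a single pre-post contrast read at visit 3. A reading taken after the packs ran out is labelled end of treatment and enters that contrast unmarked. If the blood pressure effect fades after stopping, these readings move the estimated change towards zero. The other outcomes read at visits 2 and 3 are exposed in the same way.

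**Working it through.** **Inputs.** Supply rule, dose and return of leftovers: section 11.C. Windows: Table 2, so visit 2 falls on days 21–35 and visit 3 on days 49–63. Morning visits: section 11.B. Day 0 is visit 1. Full adherence is assumed.

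**The protocol's own totals.** Packs = (interval + 3) × 2.
- Standard: (28 + 3) × 2 = 62 packs, which is 31 days of drug.
- Maximum: (35 + 3) × 2 = 76 packs, which is 38 days.

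Both agree with the protocol.

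**Visit 2 on day 28, visit 3 booked for day 56, 62 packs.** The last covered day depends on when the new packs are started:
- both packs taken on day 28: days 28–58 are covered;
- first pack on the evening of day 28: covered to the first pack of day 59;
- first packs on day 29: days 29–59 are covered.

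Days without drug before a morning visit:

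| Visit 3 attended on | Both packs on day 28 | Started that evening | Started on day 29 |
| --- | --- | --- | --- |
| up to day 59 | 0 | 0 | 0 |
| day 60 | 1 | 0.5 | 0 |
| day 61 | 2 | 1.5 | 1 |
| day 62 | 3 | 2.5 | 2 |
| day 63 | 4 | 3.5 | 3 |

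At two packs a day, the longest gaps are 8, 7 and 6 packs.

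**Visit 2.** Packs from day 0 with visit 2 booked for day 28 give the same gaps on days 32–35.

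**Where there is no gap.** A visit up to 3 days late is covered. So is a visit attended as booked at any interval up to 35 days: booked for day 63 from day 28, the patient has 76 packs. Missed doses also stretch the supply. Dosing on days 28–62 needs 35 × 2 = 70 packs, and 62 / 70 = 89%, so at about 89% adherence or lower the 62 packs last to a day-63 visit.

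**If dosing stops strictly after 56 days.** Dosing on days 0–55 leaves visits on days 57–63 between 1 and 7 days off drug; dosing on days 1–56 leaves them 0 to 6 days off.

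**Early bookings.** Four days applies to a visit booked for day 56. With visit 2 on day 21 and visit 3 booked 28 days later (day 49), 62 packs cover days 21–51. A visit on day 63 is still in window, but 63 − 1 − 51 = 11 days off drug.

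**The case against.** The strongest reply is that the dispensing rule already reflects the window. The 35-day maximum is the last in-window day for visit 2 counted from day 0, and for visit 3 counted from day 28, and the reserve comes on top. That is true for lateness known when the packs are handed out. It does not help when the patient is booked for 28 days and then comes late, because the quantity follows the booked date.

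A second reply is that treatment is planned for 56 days, so a patient supplied to day 58 or 59 has had the whole course, and nothing requires the visit 3 reading to be on drug. The absence of such a requirement is a fair point. But the dispensing rule runs to the next visit and beyond, so it implies dosing until visit 3, and a strict 56-day stop makes the gap longer.

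Third, several things must coincide: a 28-day booking, unannounced lateness of 4 to 7 days, and good adherence. Section 9 has staff arrange schedules individually, and Table 2 has adherence checked at visits 2 and 3. This stands, and it makes the case a contingency. Monitoring would record a run-out, but it neither prevents one nor keeps the reading out of the FAS. How to analyse such readings may well be left to an analysis plan; the amount dispensed is fixed here.

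**Conclusion.** The concern holds and is minor. For a visit booked for day 28 or day 56 and attended 4 to 7 days late without notice, the gap is 1 to 4 days if both packs are taken on the day of dispensing, 0.5 to 3.5 days if dosing starts that evening, and 0 to 3 days if it starts the next day. These figures assume full adherence, morning visits and no interim resupply.

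The protocol gives neither the share of late attenders nor the time over which the effect wears off, so the number of patients affected and the size of any dilution cannot be computed. The direction, towards no change, depends on the effect fading after the last dose. The study is small, has a single arm and is exploratory, so the point is worth correcting because the correction is cheap.

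**What to change.** State in section 11.C that dosing continues until visit 3. At each dispensing, supply enough to reach the last in-window day of the next visit, keeping the current amount where that is larger:
- visit 1: 35 × 2 = 70 packs;
- visit 2: (63 − day of visit 2) × 2 packs, which from day 28 is 35 × 2 = 70.

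From day 28 with same-day dosing, 70 packs cover days 28–62, so a morning visit on day 63 follows no day without drug.

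**Cost.** On the standard schedule this is 70 − 62 = 8 more packs per dispensing, 8 × 2 = 16 per patient and at most 16 × 30 = 480 for 30 patients; more if the next visit is booked early. The 76-pack maximum has to rise when visit 2 falls on days 21–24: (63 − 24) × 2 = 78 up to (63 − 21) × 2 = 84. From day 25, (63 − 25) × 2 = 76 is enough. Late attenders would be dosed up to 7 days past day 56, so the 56-day treatment period needs matching wording. Unused packs are already returned, and no extra patients, visits or tests are needed.
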